**Fig. 2 Fig2:**
[figure not shown]
Patient assessments. Notes: HRV = heart rate variability, BVP-A = blood volume pulse amplitude, S = therapeutic session, T = overall timing of assessment, Q = timing of questionnaire assessment, D = timing of distress assessment, C = timing of cortisol /α-amylase assessment, H = timing of cardiovascular recordings, I = timing of interview

### Caregiver procedures

If the caregiver has given consent to participate, we will contact the caregiver proposed by the patient either in person or by phone after completion of the last session. The reason for the inclusion of caregiver evaluations in the study design is the possibility to gather indirect information on the endurance of effects. Caregivers will be provided with all relevant information concerning their study participation and asked to sign the consent form. Subsequently, they will participate in a brief structured interview on their retrospective evaluation of treatment quality (T1). We will ask for permission to contact the caregiver again after 8 weeks (T2). On this follow-up assessment, caregivers will answer the same questions as at T1 in a telephone interview. If the caregiver expresses intense distress or unease, we will offer to postpone the appointment. To be included in the analysis, follow-up assessments (T2) need to be completed within 16 weeks after T1.

### Interventions

The intervention in the EG is a newly developed music therapy technique specifically designed to address psycho-spiritual needs in an end-of-life care context by using a creative-arts based technique (“Song of Life”). The core element of SOL is a biographically meaningful song, based on the “Song of kin” music therapy technique of neonatal care [47, 48]. The song of kin is a parent-selected song performed as a lullaby and synchronized with the infant’s vital signs [49]. The SOL-technique has shown to be feasible and accepted in palliative care in a recent pilot study [50]. We expect each of the three therapeutic sessions (S) to last between 20 and 35 min:S1 (Interview): The first session comprises an interview including several biographical questions with a focus on the musical background of the person. The last items specifically aim to identify the patient’s SOL, which is a song that has a high biographical relevance and the potential to arouse strong emotional reactions [47, 48, 51]. Our pilot study [51] showed that such a song is often associated with social bounds (e.g. romantic partner, children, parents), biographic events (e.g. marriage, child’s birth), or certain places (e.g. birthplace, vacation). The first session ends with the offer to perform a brief music therapy relaxation exercise using the monochord and vocal improvisation.S2 (“Song of Life”): The second session will be carried out the next afternoon to give the therapist time to prepare the patient’s SOL. The therapist uses the guitar/piano and her voice and first initiates a brief relaxation exercise accompanied by gentle sounds on the instrument in the musical key of the following song. If possible, the musical beat entrains to the patients’ breathing cycle and the therapist gradually reduces the meter [52]. If applicable, the therapist can include quotations of important sentences from the interview in S1. The music afterwards turns into a life performance of the SOL in a lullaby style. This requires the therapist to translate the original version into a slow 3/4-rhythm or 6/8-rhythm. The song performance is faded out with a diminuendo of the hummed song chorus.S3 (“Reflection”): The live performance will be recorded and edited after S2 by the therapist or study assistant, and will be handed over to the patient in S3. Therapist and patient can complete the intervention by listening together to the recording and reflect on the statements and messages. After this initial phase of free conversation, the therapist will guide the talk according to themes of a semi-structured qualitative interview on the patient’s perceptions, attitudes, and beliefs towards the strengths and weaknesses of the SOL intervention. At the end, the therapist can offer to again play a brief music therapy relaxation on the monochord.

The control group intervention consists of three sessions of relaxation exercises, carried out by the music therapists involved in this study. A professional mindfulness trainer created three standardized, consecutive exercises for supine positions for the purpose of this study. Each exercise will last for approximately 20 min. Elements of these sessions are guided relaxation, focused breathing, and mindfulness. The techniques will not contain musical elements and will not target biographical or spiritual themes. Therapists at both study sites have been trained in conducting the SOL and relaxation treatment before the onset of the intervention period.

As study participation is voluntary, the patient can cancel the intervention at any given point (e.g., due to worsening physical states). In this case, it remains the patient’s decision whether the data collected up to this point should be deleted. If the patient consents, self-report data on the primary and secondary outcomes (see below) will be collected together with reasons for drop-out.

### Outcomes

Previous psychosocial research often used generic quality of life measures, palliative performance, or the concept of dignity as the primary outcome and faced difficulties in identifying significant effects on these constructs (which were operationalized including items on functional or physical state) [53]. The present SOL intervention is assumed to work on an emotional and spiritual level. Therefore, improvement in the psychological domain of quality of life (a1) is chosen as the primary patient endpoint, while the secondary outcomes encompass spiritual well-being (b1), ego-integrity (b2), general quality of life (b3), distress (b4), and the retrospective evaluation of the interventional benefits (b5). To gather additional information about the mechanisms underlying a potential effect, we will assess psychobiological markers of stress (c1) as well as subjective beliefs and attitudes towards the treatments in a qualitative interview (c2). As stated above, the family caregiver’s perspective will be captured both after the intervention and 8–16 weeks later (d1). A study assistant and a doctoral student will carry out all outcome assessment, including questionnaires, photoplethysmography, saliva samples, and caregiver interviews.

Table 1 gives an overview of the study outcomes for patients and family caregivers. The timing of assessments can be found in Fig. 2.

**Table 1 Tab1:** Study outcomes

	Primary outcome	Secondary outcomes	Exploratory analyses
Patient	• a1: Quality of life – psychological (MQOL-R, 4 items, T0-T1)	• b1: Spiritual well-being – meaning/peace (FACIT-Sp, 8 items, T0-T1) • b2: Ego-integrity (Brief Measure of Generativity and Ego-Integrity, 5 items, T0-T1) • b3: Quality of life - global (MQOL-R, 1 item, T0-T1) • b4: Distress (NCCN Distress Thermometer, 1 item, pre-post each session) • b5: Retrospective evaluation (Feedback Questionnaire, 8 Items, T1 only)	• c1: Biomarkers of stress: ▪ HPA-axis (cortisol) ▪ Sympathetic nervous system (salivary α-amylase, peripheral blood flow) ▪ Parasympathetic nervous system (HRV) • c2: Strengths and weaknesses of the intervention; Beliefs about working mechanisms (qualitative interview)
Caregiver		• d1: Retrospective evaluation (Feedback Questionnaire, 12 items, T1-T2)	

*FACIT-Sp* Functional Assessment of Chronic Illness Therapy – Spiritual Well-being, *MQOL-R* McGill Quality of Life Questionnaire Revised, *NCCN* National Comprehensive Cancer Network, *HPA* hypothalamic-pituitary-adrenal, *HRV* heart rate variability, *T0* baseline assessment, *T1* post intervention assessment

#### Primary outcome

1) The *psychological subscale* of the *McGill Quality of Life Questionnaire - Revised (MQOL-R)* [54, 55] will be used to measure changes in emotional well-being at the end of life from T0 (pre intervention) to T1 (post intervention). The MQOL was originally developed in 1996 for patients with life-threatening diseases and has recently been shortened and revised [56]. The current version consists of 14 items and four subscales (physical, psychological, existential, social), which all showed acceptable internal consistency. Confirmatory factor analysis provided support for the assumed measurement structure [56]. The psychological subscale contains 4 items on 11-point scales asking for issues related to depression and anxiety in the past 2 days.

#### Secondary outcomes

1) We will assess changes on the 8-item *meaning/peace-scale* of the *Functional Assessment of Chronic Illness Therapy - Spiritual Well-Being (FACIT-Sp)* to measure non-religious aspects of spiritual well-being. The FACIT-Sp is an extended version of the *Functional Assessment of Cancer Therapy – General (FACT-G)* and is commonly used in cancer and palliative care research. Adequate psychometric properties were identified for both the FACT-G [57] and the FACIT-Sp [58]. We will reduce the time frame in the items from seven to three days.

2) According to Erikson’s stages of psychosocial development [21], to gather acceptance and a sense of meaning regarding one’s past life is an important developmental task in the last stage of life. We will measure progress in this adaption process using the 5-item *ego-integrity subscale* of the *Brief Measure of Generativity and Ego-Integrity* [59]. The questionnaire’s factor structure has been confirmed in a validation study.

3) The *MQOL-R’s overall quality of life* single-item scale [56] will be used to briefly measure treatment effects on general well-being. The item asks for overall quality of life during the last 48 h from *very bad (0)* to *excellent (10).* The abovementioned secondary outcomes b1 to b3 will all be assessed at baseline (T0) and after completion of session 3 (T1).

4) Additionally, we will utilize a modified version of the *NCCN Distress Thermometer* [60] before and after each session to monitor changes in momentary distress (D1-D6, Fig. 2). The single-item scale has a response range from *no distress (0)* to *extreme distress (10)*. The original version is a commonly used screening instrument in cancer care and research asking for distress in the past week, while an existing modified and more change-sensitive version asking for current distress will be used in the present study [61].

5) Post-intervention assessment (T1) will be complemented by a shortened and modified version of the retrospective *Feedback Questionnaire*, previously used in dignity therapy research [17]. We will use eight items on a 5-point scale covering aspects of the patient’s subjective perception of treatment effects. For each item, patients can state reasons for their rating in an open format.

#### Exploratory analyses

1) In order to understand more about the mechanisms underlying a potential treatment effect, we will collect and record psychobiological data on stress reactivity during session 2 (which contains the performance of the SOL). Due to the paucity of research regarding the effects of psychosocial interventions on biological stress markers in palliative care, we decided to rather explore trajectories in a mechanistic approach than to state explicit hypotheses. The psychobiological assessments in this study aim at monitoring states and changes in the following regulatory systems:Hypothalamic-pituitary-adrenal (HPA) system via salivary cortisolSympathetic nervous system (SNS) via salivary α-amylase and peripheral blood flowParasympathetic nervous system (PNS) via heart rate variability (HRV)

It is important to note that these stress markers will be collected non-invasively by means of saliva samples (cortisol, α-amylase) and photoplethysmography (blood flow, HRV) aiming to minimize patient burden. The timing of assessments is depicted in Fig. 2. Saliva samples will be collected at three measurement times during session 2 (C1-C3, Fig. 2) for the analysis of cortisol and α-amylase. These therapy sessions and data collection will preferably take place at standard times during the day (between 2 pm and 6 pm).

Cortisol is the end-product of a cascade of neuroendocrine responses to physically or psychologically challenging situations. As free cortisol concentration in saliva reaches its peak approximately 20 min after central activation of the HPA axis in response to a stimulus [62], the measurement points C1-C3 correspond to:  20 min. before Baseline (C1), pre intervention (C2), and post intervention (C3). The Cortisol Salivette® (Sarstedt, Nümbrecht, Germany) will be used for saliva sampling. Patients are asked to chew on a small synthetic swab for 1 min for each saliva collection. Swabs will be placed in sterile plastic centrifugation tubes. All samples will be stored at − 80 °C at the laboratory of the Institute of Medical Psychology (IMP), where they will later be centrifuged and analyzed using standard commercially available ELISA.

We will additionally calculate concentrations of salivary α-amylase (sAA) from the same saliva samples as a measure of SNS activity. sAA is an enzyme mainly secreted by the parotid glands in response to adrenergic innervation and has thus been studied as a proxy for the sympathetic modulation of acute responses to stress [63–65]. Short-term increases in sAA release were observed in psychologically challenging situations [66] and in response to pharmacological stimulation of adrenergic receptors [67].

We acknowledge the dependence of the endocrine biomarkers on exogenous glucocorticoids, chemotherapy, and opioid administration [68, 69]. The majority of patients in palliative care requires medication intake from multiple of these classes. Our interest, however, lies not in the absolute cortisol levels, but in the reactivity to the interventions provided, and hence, in the exploration of intra-individual change over time.

Additionally, we will use photoplethysmography for non-invasive, continuous recordings of participants’ autonomic response before, after, and during the interventions. A Blood Volume Pulse Sensor (biosignalplux, Lisbon, Portugal) will be placed on the index fingertip of the non-dominant hand, detecting relative changes in peripheral circulation [70]. The time point of the R-wave is used to extract inter-beat-intervals (IBI) between successive heartbeats in milliseconds. HRV parameters can be derived for consecutive time segments of 5 min duration [71]. High-frequent HRV is in indicator for vagal modulation of cardiac outflow [72–75] and has shown to correspond to self-ratings of relaxation and well-being in response to psychosocial interventions in palliative care [76, 77].

The amount of peripheral blood flow in the fingertips’ capillaries is predominantly subject to adrenergic innervation by the SNS, leading to tonic vasoconstriction. An increase in blood volume pulse amplitude (BVP-A) is therefore associated with a reduction in sympathetic arousal. Thus, the mean BVP-A of each 5-min segment will be considered an inversely related index of vascular sympathetic tone [70, 78–80]. We will continuously record the first 20 min of session 2 (H1) which includes the live-performance of the chosen SOL, and another 5-min segment 20 min later (H2), in parallel to saliva sample C3 (Fig. 2).

2) After an individual reflection conversation about the SOL and listening to the music, the study therapists will guide the second part of session 3 on the basis of a semi-structured interview (I1, Fig. 2). Open questions will address perceived strengths and weaknesses of the treatment, possible adverse effects as well as subjective explanations for potential effects. Our goal is to gain additional insights about the underlying mechanisms of the SOL intervention. The qualitative interview will last for approximately 10 min and will be carried out and recorded only in the EG.

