### Study design

The study utilizes a prospective, randomized controlled design with two parallel arms. Patients will be randomly assigned to three sessions of either music therapy (EG) or relaxation exercises (CG). We will not give information about which of the two alternative treatments is the experimental and which is the control condition. Hence, patients will be blinded with regard to the study hypotheses. It will not be possible to blind the therapists and outcome assessors, but all data will be assessed by persons different than the study therapists (i.e. study nurse, doctoral student). We will use a computer-based block randomization procedure with a block size of 8. A random sequence for group assignment will be created before the first patient is randomized. Based on this sequence, we will use the SNOSE-method [46] to conceal allocation. We expect benefits and improvements in both treatment groups with a superiority of the SOL intervention. The study design is summarized in Fig. 1.

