### Data monitoring and management

Data collection and conduction of trial will be monitored by the principal investigators. Adverse or unintended effects of interventions or conduct will be reported and managed in standard palliative care. In order to protect confidentiality, all data and biomaterial will be collected and stored for 10 years in a pseudonymized form at the Center for Psychosocial Medicine at University Hospital Heidelberg. Only the principal investigators will have access to the assignment key. No third parties are allowed inspection of personal data. After the end of the research project, data will be published in online repositories in an anonymized form.

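### Direct questioning about adverse effects is specified only for the music arm, by the treating therapist in session 3, so directly elicited adverse effects are not comparable between arms

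*Protocol article*

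**What the plan says.** Exploratory analyses, item 2, of the protocol article states that "the study therapists will guide the second part of session 3 on the basis of a semi-structured interview", and that its open questions cover "possible adverse effects as well as subjective explanations for potential effects". The interview "will be carried out and recorded only in the EG". The description of session 3 under Interventions confirms who leads it: "the therapist will guide the talk according to themes of a semi-structured qualitative interview". The stated purpose is explanatory: "Our goal is to gain additional insights about the underlying mechanisms of the SOL intervention". Table 1 lists the interview as exploratory item c2, and Data analysis assigns it to qualitative content analysis.

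Two other statements bear on this. Study design concedes that therapists and assessors cannot be blinded, and offers as a safeguard that "all data will be assessed by persons different than the study therapists". Data monitoring and management gives the general provision on harm: "Adverse or unintended effects of interventions or conduct will be reported and managed in standard palliative care". That provision is not limited to one arm. It names no way of asking, no time point and no comparison between arms.

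**The concern.** How often an adverse effect is recorded depends on whether someone asks, who asks and when. Here all three are fixed for one arm only. Control patients have no described counterpart to the question. Experimental-group patients are asked by the person who treated them, to whom they may be reluctant to report harm. Those who stop before session 3, possibly because of an unwanted reaction, do not reach the question.

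Tolerability is a fair question in this trial. Under Interventions, the song is selected partly for its power to stir strong emotion. Under Discussion, the relaxation comparator is expected to bring real benefit too. If interview mentions were set beside whatever control patients happen to report, the contrast would mix true differences with differences in asking.

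**Working it through.** The plan states no figure on this point, so there is nothing to reproduce. The check compares the sources of harm information by arm.

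| Source (section) | Experimental group | Control group | Collected by | Direct adverse-effect question? |
|---|---|---|---|---|
| Session 3 interview (Interventions; Exploratory analyses, item 2) | yes, if session 3 is reached | no | treating therapist | yes |
| General provision (Data monitoring and management) | yes | yes | not stated | not stated |
| Distress before and after each session (Patient procedures; Secondary outcomes, item 4) | yes | yes | non-therapist | no |
| MQOL-R, T0 and T1 (Primary outcome; Secondary outcomes, item 3) | yes | yes | non-therapist | no |
| Feedback Questionnaire at T1 with open reasons (Secondary outcomes, item 5) | yes | yes | non-therapist | none described |
| Reasons for drop-out, with consent (end of Interventions) | yes | yes | not stated | none described |

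Three things follow.

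1. **Asymmetry.** Only the first row is a described direct question, and it exists in one arm. This is positively stated, not inferred from silence.

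2. **Internal departure.** Study design says non-therapists assess all data, and Outcomes assigns all outcome assessment to non-therapist staff. The interview is listed in Table 1 as c2 but is led by the therapist.

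3. **Early stoppers.** Sample size expects about 25% dropout. With 104 patients, about 104 / 2 = 52 per arm, that is 52 x 0.25 = 13 per arm if dropout is equal. If all of it fell before the interview, about 52 - 13 = 39 experimental-group patients would be asked. The timing and balance of dropout are assumptions.

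**Can a size be given?** If true risk is equal in both arms, the apparent risk ratio is detection in the experimental group divided by detection in the control group. The document gives neither, so any value is assumed:

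- Capture 0.90 for all experimental-group patients, against 0.30, 0.50 or 0.70 in controls: ratio 0.90/0.30 = 3.00, 0.90/0.50 = 1.80, 0.90/0.70 = 1.29.
- The same, but with 25% not interviewed and captured at the control rate: (0.75 x 0.90 + 0.25 x 0.30)/0.30 = 0.75/0.30 = 2.5, and (0.75 x 0.90 + 0.25 x 0.50)/0.50 = 0.80/0.50 = 1.6.
- Equal capture in both arms, for example 0.90 and 0.90: ratio 1.00.

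These figures still ignore reluctance to report harm to one's own therapist, which lowers the numerator. If the interview simply adds to equal general reporting, pooled counts lean against the music arm. If it is relied on in place of independent questioning, missed stoppers and reluctance push the other way. The article does not say which applies, so the net direction is open.

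**The case against.** The strongest reply is that no biased comparison is planned. The interview is exploratory, aimed at mechanisms and analysed qualitatively. Harm is not an outcome in Table 1, and no count by arm is announced. A spurious difference would arise only if interview mentions were counted as events. This stands, and it makes the point a modest one.

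A reader might infer that harms cannot be compared between arms at all. The document does not support that. Distress ratings, MQOL-R scores, open comments and drop-out reasons permit a limited comparison, and a patient who stops after session 1 or 2 has already given distress ratings. Experimental-group patients who stop early miss the interview, but with consent they are still asked why they stopped.

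A reader might also infer that control patients are never asked about harm. That goes too far as well. The general provision covers both arms, and the detail of how adverse effects are elicited is something an article may leave to a full protocol that is not shown. The supportable statement is that no matching question is described.

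Finally, a reader might take the 1.8- to 3-fold ratio as the size of the bias. It rests wholly on assumed capture rates and leaves out early stoppers and under-reporting.

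What remains after these objections is the stated one-arm question, asked by the therapist, and its departure from the article's own rule on who collects data.

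**Conclusion.** The point holds in limited form. Adverse effects obtained by direct questioning are not comparable between arms, because the only described question is put to one arm, by the treating therapist, and only to patients who reach session 3. Tolerability can still be compared to a limited extent from data collected in both arms, none of which is described as a systematic adverse-effect question. No size can be given from the document, and the net direction of bias is unknown. The primary endpoint and every planned test are unaffected. This is a cheap improvement worth making. The conclusion rests on the article alone. If the full protocol already specifies a common question for both arms, what remains is to reconcile the therapist-led interview with the Study design rule and to keep its mentions out of any comparison.

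**What to change.** - Have the non-therapist outcome assessor ask one open adverse-effect item, worded identically, in both arms at T1.
- Ask the same item at the drop-out contact described at the end of Interventions, for patients who consent to it.
- Report the answers by randomised arm.
- The question may stay in the interview, where it gives useful information on a new technique. Report adverse effects mentioned only there as separate qualitative data, outside the between-arm comparison.
- Amend the Study design sentence on data collection to name the interview as an exception.

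The cost is about one minute per patient at contacts that already exist, with no added visit or staff. One limitation remains: T1 follows session 3, so experimental-group patients will already have been prompted once by the interview. The report should say so.
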